#### Stage 1 (Development Stage)

This stage will involve semistructured interviews and focus groups to obtain qualitative data for the design and content of the PUfP prototype. All participants (ie, clinicians and parents) will be sent information sheets and consent forms in advance of the interviews and focus groups. In addition to gathering parents’ experiences of decision making in CAMHS, an existing prototype of PUfP will be presented, and suggestions for content and prototype upgrades will be obtained. Focus groups are expected to last up to 90 minutes, and interviews (phone or face to face) to last up to 1 hour. The aim is to achieve saturation or involve a minimum sample of 12 interviews or 2 focus group discussions per group [56,57]. After the first 10 interviews, saturation for this study is reached once no new material emerges after further 3 consecutive interviews [58].

In the focus groups and interviews, participants will review the current prototype on materials supplied by the researcher. Feedback on all aspects of the prototype will be requested, and questions about the additional support needs and recommendations for the upgrade will be asked. In addition, the usefulness of the intervention and preference for modality will be sought. At the end of the focus groups and interviews, participants will be debriefed and advised to contact researchers with any further questions or suggestions via our contact details previously given on the information sheets.

#### Stage 2 (Pilot-Testing Stage)

The 18 sites identified will be randomly assigned to either control or 1 of the 2 intervention groups. Intervention group 1 (IG1) will receive the prospective version 1 of PUfP, which includes the *Support* and *Resources* features. Intervention group 2 (IG2) will receive version 2 of PUfP without these 2 features. The cluster randomization was completed independently of the research team, using R software guided by the balance algorithm [59]. Participant-level randomization will not be conducted for this study and parents at all selected sites will have a chance to participate in the study. The Standard Protocol Items: Recommendations for Interventional Trials (SPIRIT) diagram (see Table 1) and flow diagram (see Multimedia Appendix 1) illustrates the pathway through the trial, based on the trial protocol (version 1.3, November 14, 2018) approved by the NHS Research Ethics Committee and the Health Research Authority.

Stage 2 involves reinviting previous participants and obtaining informed consent from all the participants. Participants will be identified and recruited in identical ways as in the development stage. Participants will then be assigned to use the prototype and give feedback on usefulness, usability, and acceptability of the intervention. Up to 90 parents, and their respective clinicians, will be invited to participate in this stage with approximately 30 being allocated version 1 of PUfP, another 30 being allocated version 2, and the remaining 30 as the control group, receiving no app but subject to the same battery of questionnaires and treatment as usual. A sample ranging from 10 to 30 per arm should allow for calculations of feasibility and standardized effect sizes that are small to medium [60,61]. Power calculations, based on repeated measures, within – between comparisons among 3 groups for a single measure across two occasions, indicated that a total sample size of 30 would provide a power of 0.8 to detect an effect size of 0.3. Participants will be assigned to an intervention or control group based on the site from which they have been recruited to avoid contamination.

Participants will meet with the researcher at a time convenient to them, to complete a battery of baseline questionnaires, which consists of SDM measures, the experience of service, and decisional conflict measures. Participants will have the choice to complete these online or using paper and pencil. Depending on which group the participants belong to (IG1 and IG2), they will receive help to access the app and be given a guided tour of the app. The parent will then go away and use the app as much as they need to. Participants will complete follow-up measures about 3 months after or at dropout/discharge (whichever comes first).

**Table 1 table1:** SPIRIT diagram for the Power Up for Parents feasibility trial.

Time point		Study period				
		Enrollment	Pretest	Intervention	Posttest	End of Study
Eligibility screen		X^a^	—^b^	—	—	—
Informed consent		X	—	—	—	—
Allocation		X	—	—	—	—
**Interventions**		—	—	—	—	—
	Intervention Group 1	—	—	X	X	X
	Intervention Group 2	—	—	X	X	X
	Control Group	—	—	—	—	X
**Assessments**		—	—	—	—	—
	Feasibility outcomes	X	X	X	X	X
	CPS-P^c^	—	X	—	X	—
	PSDM-Q-Parent^d^	—	X	—	X	—
	STAI-AD^e^	—	X	—	X	—
	DCS^f^	—	X	—	X	—
	ESQ^g^	—	X	—	X	—
	PSSUQ^h^	—	—	—	X	—

^a^Schedule and time commitment for trial participants.

^b^Not applicable.

^c^CPS-P: Control Preferences Scale for Pediatrics.

^d^PSDM-Q-Pediatric Shared Decision-Making Questionnaire.

^e^STAI-AD: Spielberger State Anxiety Inventory Form for Adults.

^f^DCS: Decisional Conflict Scale.

^g^ESQ: Experience of Service Questionnaire.

^h^PSSUQ: Post-Study Usability Questionnaire.

Clinicians will also complete an adapted version of the Control Preferences Scale (CPS) so researchers can obtain their perspective on changes in the amount of parental involvement in the child’s care and treatment decisions. It may also be important for clinicians to report any changes in the length of appointments or missed appointments and improvements in a child’s mental health.

At the end of the pilot-testing phase, participants will share their opinions on the study and, more specifically, on the intervention used and will then be debriefed and thanked for their participation.

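### Stage 1 participants, already shown the prototype and asked to help shape it, are re-invited into Stage 2 and allocated by site, so for this subset site allocation cannot prevent contamination

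*Protocol article*

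**What the plan says.** All references are to the protocol article.

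- **Stage 1 (Development Stage).** In interviews or focus groups with parents and clinicians, "an existing prototype of PUfP will be presented, and suggestions for content and prototype upgrades will be obtained". Also, "participants will review the current prototype on materials supplied by the researcher", and "Feedback on all aspects of the prototype will be requested". The target is saturation or a "minimum sample of 12 interviews or 2 focus group discussions per group". Interviews last up to 1 hour and focus groups up to 90 minutes.
- **Stage 2 (Pilot-Testing Stage), recruitment.** "Stage 2 involves reinviting previous participants and obtaining informed consent from all the participants". The next sentence adds: "Participants will be identified and recruited in identical ways as in the development stage".
- **Stage 2, allocation.** "Participant-level randomization will not be conducted for this study and parents at all selected sites will have a chance to participate in the study". The reason given is: "Participants will be assigned to an intervention or control group based on the site from which they have been recruited to avoid contamination". The three arms are app version 1, app version 2 (without the Support and Resources features) and a control arm with no app. Each has about 30 parents.
- **Recruitment, Parents.** The only preliminary exclusion that touches earlier involvement concerns other research. Stage 1 of this study is not named.
- **Planned Analysis, Stage 2.** Between-group mean differences at baseline and follow-up are planned, and the analyses feed the sample size of the future trial.

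**The concern.** Two stated rules work against each other. Allocation by site is meant to keep the arms separate, while the recruitment rule brings in people who have already seen the app, with no restriction by arm. Three things are at stake.

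1. **Feasibility figures.** Research Questions asks about consent, adherence, engagement, acceptability and usefulness, and Participation Numbers records completion of each study step. People who volunteered once and helped shape the app may be readier to consent, stay and rate it well. A future trial would not recruit mainly from such people.
2. **Usability ratings.** Re-invited parents in the app arms complete the PSSUQ on a product built partly on their own suggestions.
3. **Between-group estimates.** For re-invited parents the Stage 2 pretest is not a pre-exposure measurement in any arm, and control parents are not app-naive. The differences used to plan the trial may be too small.

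Clinicians are a second route. They take part in Stage 1 and later complete the adapted Control Preferences Scale, so a clinician at a control site may also have seen the app.

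**Working it through.** **The plan's own power figure.** Stage 2 states power 0.8 at total N = 30 for effect size 0.3 (3 groups, 2 occasions, within-between comparison). I read 0.3 as Cohen's f. The article gives neither alpha nor the correlation between occasions, so I assume 0.05 and 0.5.
- Noncentrality = f² × N × m / (1 − rho) = 0.09 × 30 × 2 / 0.5 = 10.8, with 2 and 27 degrees of freedom. Power = 0.80, so the figure reproduces.
- It depends on the assumed correlation: power is 0.49 at 0, 0.65 at 0.3 and 0.96 at 0.7. The formula ignores site clustering. The present point does not rest on this figure; it serves only as a scale.

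**How many parents.** I read the minimum as 12 interviews with parents and a similar number with clinicians. Focus-group size and the re-enrolment rate are not given.
- All 12 re-enrol in a sample of 90: 12/90 = 13%, or 4 per arm if spread evenly.
- All 12 come from the sites of one arm of 30: 12/30 = 40% of that arm.
- Ninety is an upper limit, and the article accepts 10 per arm. At 3 × 10 = 30 in total, 12 would be 40% of the whole sample.

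**How a contrast moves.** Let D be the app effect and c the fraction of D that a Stage 1 session already carries. Let sA and sC be the shares of re-invited parents in the app and control arms. Assume the session effect lasts and that all app users end at the same level.
- Difference at baseline: c·D·(sA − sC).
- Difference at follow-up: D·(1 − c·sC). This is weakened by re-invited control parents.
- Difference in change: D·(1 − c·sC) − c·D·(sA − sC) = D·(1 − c·sA). This is weakened by re-invited app-arm parents.

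With an even spread both contrasts shrink by the same factor, 1 − c·s. The values of c below are assumptions.

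| Share s | c | Loss c·s | f | Power at N = 30 |
|---|---|---|---|---|
| 13% | 0.25 | 3% | 0.29 | 0.77 |
| 13% | 0.50 | 7% | 0.28 | 0.74 |
| 13% | 1 | 13% | 0.26 | 0.67 |
| 40% | 0.25 | 10% | 0.27 | 0.71 |
| 40% | 0.50 | 20% | 0.24 | 0.60 |
| 40% | 1 | 40% | 0.18 | 0.37 |

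At N = 90 and s = 13%, power by the same formula stays above 0.99.

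**Feasibility rates.** Observed rate = p·r1 + (1 − p)·r0, so the bias is p·(r1 − r0). At p = 13%, each 10-point gap between re-invited and new parents moves the observed rate by 1.3 points. With assumed retention of 95% and 70%: (12 × 0.95 + 78 × 0.70)/90 = 66/90 = 73.3%, against 70% in new parents.

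**The case against.** The strongest case against is that the exposure is slight and the trial is not built on its contrasts. Stage 1 offers one supervised look at a prototype. In Stage 2, app-arm parents get a guided tour and free use until follow-up at about 3 months. Analysis is mainly descriptive, with some exploratory testing. Repeated involvement of users is a deliberate part of co-design, and re-invitation is not enrolment, since fresh consent is required. The inclusion and exclusion criteria are preliminary, and a fuller protocol could add a flag or sensitivity analysis.

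Much of this stands as to size. If a session carried a quarter of the app effect and the 12 parents were spread evenly over 90, f would move only from 0.30 to 0.29. It does not remove the point. The article states a recruitment rule, rather than leaving one open, and that rule conflicts with its reason for site allocation. The effect on consent, retention and usability figures needs no carry-over of the app effect at all.

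Four stronger readings are tempting but not supported:
- **The safeguard fails for the whole trial.** It fails only for re-invited people; between newly recruited parents it works as intended.
- **The contrasts lose a quarter or more.** That needs about twice the stated minimum of parents, or strong clustering or low recruitment, and also a session worth the full app effect.
- **Version 2 parents have seen the features withheld from them.** The article does not say which features the Stage 1 prototype contained; this is an inference from feedback being sought on every aspect.
- **These quantities decide whether the trial goes ahead.** The progression criteria are in an appendix that is not shown.

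**Conclusion.** The point holds for the re-invited subset. As written, the plan can place people who saw and helped shape the app in the no-app arm, and count them in the consent, retention and usability figures. The direction is plausible: feasibility figures too favourable and between-group differences too small. The size cannot be fixed from the article. About 12 parents, 13% of 90, is the figure if only the minimum number of interviews is held and all those parents re-enrol. Fewer re-enrolling lowers it; more interviews, low recruitment or clustering in one arm raises it. The 13% loss of contrast at that share is a ceiling, because it treats one session as equal to the whole app effect. The worry is sounder for the feasibility and usability figures than for the contrasts. It merits a change because the remedy is simple and the figures feed the planning of the next trial.

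**What to change.** - **Parents not yet enrolled.** Do not count Stage 1 interview or focus-group participants in the Stage 2 between-arm comparison or in the feasibility proportions. Invite them only to give feedback on the revised app, outside the 90.
- **Parents already enrolled.** Record Stage 1 participation by arm, for parents and clinicians. Report feasibility proportions, PSSUQ and between-group estimates with and without them, and use the results without them to plan the future trial.
- **Timing.** The Results section says that interviews and baseline collection are both in progress, so the record should start now.

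The cost is a flag variable, one sentence on who is counted and possibly an amendment to the approved protocol. About a dozen fewer parents would be analysed. If 12 of 90 are not replaced, 78 remain (26 per arm, within the article's range of 10 to 30), and intervals widen by a factor of √(90/78) = 1.07, about 7%, ignoring clustering.

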**Methods:**

A 2-stage process, consisting of the development stage and pilot-testing stage of the initial PUfP prototype, will be conducted. At the development stage, a qualitative study with parents and clinicians will be conducted. The interviews will aim to capture the experience of making CAMH decisions, preferences for involvement in SDM, and determine situations within which PUfP can be useful. At the pilot-testing stage, up to 90 parents and their clinicians will be invited to participate in the testing of the prototype. Parents will be randomly allocated to receive the intervention or be part of the control group. This study design will allow us to assess the acceptability and usefulness of PUfP in addition to examining the feasibility of a prospective randomized trial. Clinicians’ perceptions of the prototype and how it has influenced parents’ involvement in SDM will also be examined.

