## Methods

### Design

This a 2-stage study involving a development stage (stage 1) where the intervention will be user-tested by clinicians and parents, and suggestions will be obtained for usage and upgrading of the prototype. The pilot-testing stage (stage 2) is a 3-arm, cluster randomized pilot trial with parents accessing CAMHS.

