## Results

Recruitment began in January 2019 and is scheduled to last for 10 months. Interviews and baseline data collection are currently in progress, and to date, 11 CAMH sites have been recruited to take part in the study. It is anticipated that data collection will be completed by October 2019.

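### The stated power of 0.8 with 30 parents makes no allowance for the randomisation of sites (minor, wording only)

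*Protocol article*

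**What the plan says.** The Design section says that Stage 2 "is a 3-arm, cluster randomized pilot trial with parents accessing CAMHS". The Stage 2 section under Procedure and Materials gives the unit of randomisation: "The 18 sites identified will be randomly assigned to either control or 1 of the 2 intervention groups", and "Participant-level randomization will not be conducted for this study".

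On sample size, the same section says: "Up to 90 parents, and their respective clinicians, will be invited to participate in this stage", with about 30 per arm. It cites references for a range of 10 to 30 per arm. It then reports power calculations "based on repeated measures, within – between comparisons among 3 groups for a single measure across two occasions", which "indicated that a total sample size of 30 would provide a power of 0.8 to detect an effect size of 0.3". It gives no ICC, cluster size, design effect, alpha or pre-post correlation, and does not name the effect-size metric.

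The Results section reports that "to date, 11 CAMH sites have been recruited to take part in the study". The Methods part of the abstract describes the allocation differently: "Parents will be randomly allocated to receive the intervention or be part of the control group".

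The Planned Analysis section (Stage 2) says that results will be mostly descriptive with some exploratory significance testing. It also says that the standard deviations and intraclass correlations estimated here will feed the sample size of the later RCT.

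**The concern.** When sites are randomised, parents from the same site may resemble one another, and the comparison between arms rests on the number of sites as well as the number of parents. A power figure for independent parents then describes a different design. The described calculation shows no sign of an allowance for clustering, although the article expects to estimate an intraclass correlation from the same data.

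The stakes are modest. A total of 30 is exactly 10 per arm, the low end of the range cited just before. A reader could take the sentence to mean that a shortfall to about 30 parents would still leave 80% power for the exploratory comparisons, and could read a null result in that light. The abstract adds to the confusion by naming parents as the randomised unit.

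**Working it through.** **Inputs from the article:** 3 groups, 2 occasions, total N = 30, effect size 0.3, stated power 0.8; 18 sites identified and assigned, 11 recruited to date; up to 90 parents.

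**Assumed, because not stated:** alpha 0.05; effect size is Cohen's f; pre-post correlation rho = 0.5; ICC of the pre-post change 0.05 to 0.10 (0 and 0.20 as outer values); equal site sizes; no dropout.

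**1. Reproduce the stated figure.** For the group-by-time interaction with independent parents, lambda = f² × N × m / (1 − rho), where m is the number of occasions:

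lambda = 0.09 × 30 × 2 / 0.5 = 10.8, with df1 = (3 − 1)(2 − 1) = 2 and df2 = 30 − 3 = 27.

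The noncentral F gives power 0.8004. At N = 29 it is 0.784, so 30 is the smallest total that reaches 0.8. Other correlations do not give 0.8 at N = 30: 0.648 at rho = 0.3, 0.720 at 0.4, 0.885 at 0.6, 0.957 at 0.7. At rho = 0.5, a between-groups test gives 0.343 and a time main effect gives 0.886. The independent-parent interaction is therefore the natural reading, and it has nothing in reserve for a design effect.

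**2. Allow for sites.** Divide lambda by DE = 1 + (N/J − 1) × ICC for J sites. Take df2 either as 27 (design effect alone) or as J − 3 (site-level df): 18 − 3 = 15, or 11 − 3 = 8.

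Example with 18 sites and ICC 0.05: N/J = 30/18 = 1.67; DE = 1 + 0.67 × 0.05 = 1.033; lambda = 10.8/1.033 = 10.45. Power is 0.787 on 27 df and 0.746 on 15 df.

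Power at N = 30:

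| Sites | ICC | DE | Design effect alone | Site-level df |
|---|---|---|---|---|
| 18 | 0 | 1.000 | 0.800 | 0.760 |
| 18 | 0.05 | 1.033 | 0.787 | 0.746 |
| 18 | 0.10 | 1.067 | 0.773 | 0.731 |
| 18 | 0.20 | 1.133 | 0.746 | 0.704 |
| 11 | 0 | 1.000 | 0.800 | 0.675 |
| 11 | 0.05 | 1.086 | 0.765 | 0.637 |
| 11 | 0.10 | 1.173 | 0.730 | 0.603 |
| 11 | 0.20 | 1.345 | 0.667 | 0.542 |

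**3. Total N for power 0.8** at ICC 0.05 to 0.10: with 18 sites, 31 to 33 (design effect alone) or 35 to 37 (site-level df); with 11 sites, 33 to 37 or 47 to 57.

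**4. Power at the planned maximum, N = 90,** with site-level df: 0.991 to 0.979 with 18 sites and 0.954 to 0.897 with 11 sites (ICC 0.05 to 0.10). At ICC 0.20 it is 0.938 and 0.768.

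**The case against.** The case for leaving the sentence alone has several parts, and most of them limit the point without removing it.

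- **This is a feasibility pilot.** Analyses are mainly descriptive, significance tests are exploratory, and feasibility is judged against preset criteria. No confirmatory test rests on the 0.8. This stands.
- **A reader might infer that the figure will mislead the planning of the full RCT.** The documents do not support that: the Planned Analysis section bases the later sample size on the standard deviations and intraclass correlations estimated here.
- **A reader might infer that the pilot is too small.** It is not, for this effect. The aim is up to 90 parents, and power there is about 0.90 or more at ICC 0.05 to 0.10. Even at 60 parents with site-level df it is 0.953 to 0.931 with 18 sites and 0.877 to 0.816 with 11. The range of 10 to 30 per arm also has its own cited justification.
- **Much of the fall comes from the choice of df.** With 18 sites, site-level df alone take power to 0.76 at ICC 0, while the design effect alone costs only 1 to 3 points at ICC 0.05 to 0.10. The article fixes no model or df rule, so both sets of figures belong in the account. Both are below 0.8 for any positive ICC.
- **Eleven sites is an interim count.** Recruitment was continuing, so the 11-site figures show a possible outcome, not an expected one.
- **The inputs to the reproduction are assumed.** At rho = 0.6, with 18 sites, ICC 0.05 and site-level df, power at N = 30 is 0.84. But rho = 0.6 gives 0.885 for independent parents, so it does not explain the printed 0.8.

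**Conclusion.** The point holds as a minor error of statement. The power of 0.8 at a total of 30 matches a calculation for independent parents, and nothing in the article suggests an allowance for randomising sites. The shortfall at 30 parents with 18 sites is about 1 to 3 percentage points with a design effect alone and 5 to 7 with site-level df (ICC 0.05 to 0.10). With 11 sites it would be about 4 to 7 or 16 to 20 points. Unequal site sizes would lower power further.

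These sizes rest on alpha 0.05, Cohen's f, a correlation of 0.5 and an assumed ICC, none of which the article gives. The omission itself is less dependent on them: the described test has no clustering term, and the independent-parent calculation reaches 0.8 at exactly the stated total. Recruitment, the later RCT and the pilot's main conclusions are not put at risk.

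**What to change.** Any one of these would do for the power sentence:

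- Restate the power for the cluster design, with the number of sites and the assumed ICC, correlation, alpha, effect-size metric and df rule, preferably at the planned sample of up to 90. For example, with 18 sites, site-level df and an assumed ICC of 0.05 to 0.10, 90 parents give power of about 0.98 to 0.99 for f = 0.3, at correlation 0.5 and alpha 0.05.
- Keep the sentence, and add that it is for independent participants, ignores clustering and does not apply to the cluster design.
- Delete it. The pilot does not need it.

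The second and third options avoid writing an assumed ICC into a study that sets out to estimate one.

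Separately, correct the abstract so that it says sites are randomised and parents are allocated according to their site.

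The cost is a few words and, if the figure at 30 is restated, a less favourable number. No extra parents or sites are needed, and no analysis changes.
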